|  | Clinical Study Protocol |  |
| --- | --- | --- |
|  | EudraCT No. | 2017-005065-47 |
|  | Investigational Medicinal Product | ILB |
|  | Study Code | TM-105 |
|  | Protocol Version and Date | Final version 1.5 2019-06-25 |

| Study title  A single-centre, open single-arm study where the safety, tolerability and efficacy of subcutaneously administered ILB will be evaluated in patients with Amyotrophic Lateral Sclerosis | | |
| --- | --- | --- |
| **Indication** | Amyotrophic Lateral Sclerosis (ALS) |  |
| **Development Phase** | IIa - pilot |  |
| **Design** | Open, single-arm |  |
| **Test treatment and dosage** | ILB (20 mg/ml) for subcutaneous injection |  |
| **Duration of treatment** | Weekly doses of 1 mg/kg, 5 doses in total |  |
| **Protocol signatories** | [name], Sponsor’s Representative  [name], PhD, Principal Investigator |  |
|  |  |  |
|  |  |  |

*The following amendments have been made to the Final Clinical Study Protocol:*

| **Amendment No.** | **Date of Amendment** | **Revised protocol version** |
| --- | --- | --- |
| 1: In response to comments by MPA, Dnr 5.1-2018-21788 | 02 May 2018 | Version 1.1 |
| 2: Addition of Riluzole and Lamotrigine as prohibited concomitant medication, exclusion criteria and reason for permanent withdrawal. | 15 May 2018 | Version 1.2 |
| 3. Rephrasing of inclusion criterion 5 and exclusion criterion 9 to allow patients to fulfil these criteria before the study drug administration. | 23 August 2018 | Version 1.3 |
| 4. Replacing inclusion criterion 6 with exclusion criterion 12, to clarify that only patients with clinically significant abnormal PK-INR, fibrinogen, von Willebrand factor and APTT at screening should be excluded, and addition of potential interim analysis, | 17 December 2018 | Version 1.4 |
| 5. Administrative changes of the administrative structure and section added about pregnancy reporting | 25 June 2019 | Version 1.5 |

# STUDY SYNOPSIS

| **Study Title**  A single-centre, open single-arm study where the safety, tolerability and efficacy of subcutaneously administered ILB will be evaluated in patients with Amyotrophic Lateral Sclerosis | |
| --- | --- |
| **Study code**  TM-105 | **EudraCT No**  2017-005065-47 |
| **Study period**  Estimated date of first subject enrolled: Q2 2018  Estimated date of last subject completed: Q3 2019 | **Phase of development**  Phase IIa - pilot |
| **Study design and duration**  This is a Phase IIa single-centre, open single-arm study in patients with Amyotrophic Lateral Sclerosis.  Eligible subjects will be administered weekly doses of 1 mg/kg ILB. A total of 5 subcutaneous (s.c.) doses will be administered at the study clinic. The study consists of 10 visits; One 2-part screening visit, 5 IMP administration visits, and 3 follow-up visits. Each individual patient’s study participation will be approximately 4 months, including the screening and follow-up visits. | |
| **Number of patients planned**  15 patients | |
| **Objectives and endpoints**  Primary objective  The primary objective of the study is to evaluate the safety and tolerability of ILB in patients diagnosed with ALS.  *Primary endpoints*   - Frequency, seriousness and intensity of Treatment-emergent Adverse Events (TEAEs) - Physical examination - Vital signs - Electrocardiogram (ECG) recordings - Safety laboratory measurements: clinical chemistry, haematology including activated partial thromboplastin time (APTT)   Secondary objective  The secondary objective of the study is to evaluate efficacy of ILB in patients diagnosed with ALS.  *Secondary endpoints*   - Functional rating with ALS Functional Rating Scale – Revised (ALSFRS-R) - Functional rating with Norris scale - Evaluation of ALS biomarker Neurofilament Light chain (NFL) - Evaluation of biomarkers for neurological disorders (see 11.4.2) - Pulmonary function (FVC) - Quality of Life (QoL) - Autonomous symptoms - Levels of Hepatocyte Growth Factor (HGF) - Pharmacokinetic measurements of ILB in plasma - Changes in APTT (effect APTT)   Exploratory objectives (optional/to be decided)   - To evaluate the effect of ILB on levels of *e.g.* growth factors, cytokines and biomarkers in plasma and cerebrospinal fluid (CSF). | |
| **Safety and efficacy assessments**  Safety:   - AE assessments will start at administration of the first dose of ILB. - Physical exam will be obtained at all visits. On the days of ILB administration (Visit 2 to Visit 6), physical examination will be obtained before dosing. - Vital signs (blood pressure, heart rate and body temperature) will be obtained at all visits. - 12-lead ECG will be obtained at Visit 1 and Visit 7. - Lab tests (clinical chemistry, haematology, haemostatis) will be obtained at all visits. On the days of ILB administration (Visit 2 to Visit 6), lab tests will be obtained before dosing.   Efficacy:   - The investigator will complete the ALS Functional Rating Scale - Revised (ALSFRS-R) at all visits. On the days of ILB administration, rating scales will be completed before dosing. - The investigator will complete the Norris functional rating scales at all visits. On the days of ILB administration, rating scales will be completed before dosing. - Blood and cerebrospinal fluid (CSF) samples for evaluation of the ALS biomarker Neurofilament Light chain (NFL) will be obtained at Visit 1 after eligibility is confirmed and at Visit 7. - Blood and CSF samples for analysis of biomarkers for neurological disorders (see 11.4.2) will be obtained at Visit 1 after eligibility is confirmed and at Visit 7. - Respiratory function (FVC) will be evaluated at all visits. On the days of ILB administration (Visit 2 to Visit 6), respiratory function will be assessed before dosing. - Quality of Life (QoL) will be evaluated using Visual Analogue Scale (VAS)-based questionnaire filled out by patient and, if applicable, a next of kin, at Visit 1, Visit 2, Visit 4, Visit 6 and Visit 8. - Autonomous symptoms will be evaluated according to a 4-grade scale for a range of parameters at all visits. - Levels of Hepatocyte Growth Factor (HGF), pharmacokinetic measurements and effect APTT will be obtained in conjunction with the first and last ILB administration (Visit 2 and Visit 6). Blood samples will be obtained pre-dose, 30 minutes and 1, 2, 2.5, 3, 4, 6 hours after dosing. | |
| **Eligibility criteria**  Inclusion criteria:   1. Willing and able to give written informed consent for participation in the study. 2. Clinical diagnosis of Amyotrophic Lateral Sclerosis. 3. Male or female patients between 18 to 80 years of age (inclusive). 4. Forced Vital Capacity (FVC) ≥ 65% of predicted value for gender, height and age at screening. 5. Evaluated with ALSFRS-R and Norris clinical rating scales for at least the past 4 weeks before study drug administration.   Exclusion criteria:   1. Unable to understand information about the study or are expected not to collaborate with the study team. 2. Concurrent serious disease, other than ALS, at the discretion of the Investigator. 3. Pregnancy. 4. Patients of child-bearing potential not willing to use adequate double contraception with < 1% failure rate after the screening visit until the last visit. 5. Addiction to drugs or alcohol. 6. Confirmed HIV, Hepatitis B or C. 7. Known bleeding disorders or abnormal bleeding events. 8. Treatment with anticoagulant drugs warfarin and novel oral anticoagulants (NOAC) within the last 14 days prior to screening. 9. Treatment with Riluzole or Lamotrigine within the last 28 days prior to study drug administration. 10. Hypersensitivity to dextran sulfate. 11. Poor venous access. 12. Patients with clinically significant abnormal PK-INR, fibrinogen, von Willebrand factor and activated partial thromboplastin time (APTT) at screening. | |
| **Investigational Medicinal Product (IMP), dosage and mode of administration**  The active pharmaceutical ingredient of the investigational medicinal product (IMP) is dextran sodium sulfate salt, 5 kDa, 20 % sulfatation (ILB). ILB is a solution for subcutaneous (s.c.) injection and consists of 20 mg/ml ILB in 0.9% NaCl. Each glass vial contains 10 ml.  The dose administered will depend on the subject’s body weight at the second study visit, prior to the first ILB administration. ILB will be injected s.c. on alternating sides of the abdomen, thigh, or the buttock (in that order of priority). | |
| **Statistical methods**  No formal sample size calculation has been performed for this study. The proposed sample size is considered sufficient in this early phase II development to provide adequate information on the patients.  Categorical data will be presented as counts and percentages. Individual patient data will be listed by subject number and, where applicable, assessment time.  Continuous data will be summarised using descriptive statistics. The number of observations, mean, median, maximum, minimum and standard deviation will be reported. Individual patient data will be listed by subject number and, where applicable, assessment time.  Individual plasma concentration-time data of ILB will be evaluated using a validated Phoenix WinNonlin® software. The PK parameters will be calculated by non-compartmental analysis (NCA). Descriptive statistics for the assessed PK parameters will be presented for each parameter and first and last ILB administration (Visit 2 and Visit 6), as well as pooled data over the dosing days (if appropriate).  A more technical and detailed elaboration of the principal features will be presented in a separate Statistical Analysis Plan (SAP). | |

# LIST OF ABBREVIATIONS

| AE | Adverse Event |
| --- | --- |
| ALS | Amyotrophic Lateral Sclerosis |
| ALSFRS-R | ALS Functional Rating Scale - Revised |
| API | Active Pharmaceutical Ingredient |
| APL | Apoteket Produktion & Laboratorier |
| APTT | Activated Partial Thromboplastin Time |
| AUC | Area Under the plasma concentration - time Curve |
| AUC_0-t_ | area under the curve from 0 to t hours |
| AUC_inf_ | AUC from timepoint 0 until infinity |
| AUC_last_ | AUC from timepoint 0 until the last timepoint t |
| AUCtau | AUC in a dosing interval |
| BDNF | Brain Derived Neurotrophic Factor |
| BP | Blood Pressure |
| CA | Competent Authority |
| C_max_ | maximum observed plasma concentration |
| CRF | Case Report Form |
| CSF | Cerebrospinal Fluid |
| EC | Ethics Committee |
| ECG | Electro Cardio Gram |
| ELISA | Enzyme-Linked immunosorbent Assay |
| FGF | Fibroblast Growth Factor |
| FVC | Forced Vital Capacity |
| GCP | Good Clinical Practice |
| HGF | Hepatocyte Growth Factor |
| HIV | Human Immunodeficiency Virus |
| HUVEC | Human Umbilical cord Vascular Endothelial Cell |
| i.v. | intravenous |
| IB | Investigator's Brochure |
| ICF | Informed Consent Form |
| ICH | International Conference on Harmonization |
| ILB | Study drug / investigational medicinal product |
| IMP | Investigational Medicinal Product |
| kDa | kilo Dalton |
| LMW-DS | Low Molecular Weight Dextran Sulfate |
| Mw | Molecular Weight |
| PK | Pharmacokinetic |
| PK-INR | Prothrombin Complex International Normalised Ratio |
| PT | Preferred Term |
| QoL | Quality of Life |
| s.c. | subcutaneous |
| SAE | Serious Adverse Event |
| SAP | Statistical Analysis Plan |
| SDV | Source Data Verification |
| SOC | System Organ Class |
| SU | Sahlgrenska University Hospital |
| SUSAR | Suspected Unexpected Serious Adverse Reaction |
| t_1/2_ | half-life |
| TEAE | Treatment-Emergent Adverse Events |
| t_last_ | time at which the last plasma concentration was observed |
| t_max_ | Time at which Cmax was observed |
| VAS | Visual Analogue Scale |
| VEGF | Vascular Endothelial Growth Factor |
| WOCBP | Women of childbearing potential |

# INTRODUCTION

## Investigational background

Amyotrophic lateral sclerosis (ALS, also known as Lou Gehrig’s disease) is the most common motor neuron disease. It is a fatal disease, affecting most populations of neurons. The most important degeneration of neuronal cells occurs in motor neurons in spinal cord, brain stem and brain. The disease begins focally in the central nervous system and then spreads relentlessly[1]. The clinical diagnosis, defined by progressive signs and symptoms of upper and lower motor neuron dysfunction, is confirmed by clinical findings, electromyography, blood and cerebrospinal fluid (CSF) analysis. Additional testing with for instance Magnetic Resonance Imaging (MRI) excludes other conditions. The rate of progress of the disease is related to neuronal markers in CSF and blood. CSF levels of Neurofilament light chain (NFL) is the most important indicator of the activity of the disease [2-4]. The disease is heterogeneous, but most patients die of respiratory muscle weakness less than 3-5 years from symptom-onset. Like other age-related neurodegenerative diseases, ALS has genetic, metabolic and environmental triggers.

There is yet no cure for ALS, and management is focused on a combination of neuroprotective medication, multidisciplinary clinics and respiratory support. Speciality clinics for ALS emerged in the 1980s and most large centres in developed countries currently offer multidisciplinary care [5]. The disease causes severe decrease of the quality of life in both patients and next of kin [6-8]. Patients treated by ALS care teams may have higher quality of life [9] and longer survival [10]. Malnutrition and dehydration are common as ALS advances. Later therapy often includes percutaneous gastric feeding and non-invasive ventilatory support, which increases time of survival and increased quality of life of both patient and next of kin.

To date, one medication (riluzole, licensed in 1996) has been proved to prolong survival somewhat in ALS [11]. Riluzole was developed because it possesses anti-glutamatergic properties that might reduce excitotoxicity in ALS. Riluzole slowed disease progression in two randomized controlled trials [12, 13], delaying death with weeks or a few months [11]. The most common side effects are exanthema, diarrhoea, dizziness, fatigue, nausea, and somnolence. Elevation of liver enzymes can occur, but rarely to levels that are clinically meaningful. Many patients in Europe and more than half of ALS patients in the U.S. take riluzole [14].

Numerous trials have so far been unable to identify another neuroprotective agent. Researchers now aim to slow disease progression by targeting known pathophysiological pathways or genetic defects. Until better understanding of the causes and mechanisms underlying progression that lead to more robust neuroprotective agents, symptomatic therapies can extend life and improve quality of life. Palliative care programs such as hospice give emotional and physical support to patients and families throughout much of the disease course [15].

In this Phase II pilot study in ALS patients, safety and tolerability of ILB will be evaluated after repeated subcutaneous (s.c.) doses of ILB (1 mg/kg, 5 doses in total) during 4 weeks with 10-week follow-up. The secondary objective is to investigate efficacy through documentation of functional activity as assessed by clinical rating scales, respiratory function and biological markers.

## Investigational product ILB

The Active Pharmaceutical Ingredient (API) ILB is a type of low molecular weight dextran sulfate (LMW-DS). ILB is a polyanionic derivative of dextran which is a polymer of anhydroglucose which contains approximately 20 % sulfur (Figure 1). Each glucose unit in the dextran chain has approximately two sulfate groups, normally located at the second and fourth carbon of the glucose units.

Preparation of ILB is accomplished by alcohol fractionation, in which the largest molecular weight dextran sulfate precipitates first. The final product has an average molecular weight (Mw) of 5 kDa and contains molecules spanning approximately 3 - 8 kDa. It is supplied as the sodium salt which is a white to off-white powder freely soluble in water and salt solutions (> 100 mg/ml).

[figure not shown]

[figure not shown]

…

Figure 1 Chemical structure of ILB

During GMP manufacture of the Investigational Medicinal Product (IMP) ILB, the API is dissolved in sterile water with 9 mg/ml NaCl and filter sterilised to a clear solution.

## Rationale for use of ILB in ALS

HGF is a potent survival-promoting factor for motor neurons and has been suggested for ALS treatment [16, 17]. Human recombinant HGF (hrHGF) has been shown to attenuate spinal motor neuron degeneration in transgenic ALS rat models, and improve functional recovery in a non-human primate model of contusive cervical spinal cord injury [18, 19]. In a model of ALS in mice (SOD1 mutation), over-expression of HGF in the nervous system showed reduced motor neuron death and axonal degeneration as well as a prolonged life span [20]. HGF appears to be a good candidate for the treatment of ALS since it passes the blood-brain barrier (BBB) [21] and the HGF levels in ALS patients seems dysregulated [22]. ILB administration increases the plasma level of HGF in human healthy volunteers and in rats and mice [23].

Other growth factors with potential therapeutic use in ALS are vascular endothelial growth factor (VEGF) and fibroblast growth factors (FGF) [24]. VEGF treatment increases survival, delay disease onset, improve motor functions, protect motor neurons and the neuromuscular junction in studies on rodent ALS models. VEGF is an attractive therapeutic factor since it passes the blood brain barrier and is down-regulated in the late stage of ALS. Fibroblast Growth Factor (FGF) can protect motor neurons after axotomy-induced apoptosis and support neuronal regeneration. Sulfated polysaccharides, like ILB, have been shown to bind and affect levels and potentiate VEGF, BDNF and FGF signalling/effects [25].

In conclusion, based on nonclinical data it is possible that a positive effect of ILB in ALS would be mediated through an increase of tissue growth actors.

## Risk and benefit assessment

So far, five clinical studies have been conducted with ILB administered intravenously (i.v.) or subcutaneously (s.c.) in 79 subjects in doses up to 24 mg/kg; four studies in healthy volunteers (n=69) and one Phase-II study in diabetic patients (n=10) in association with standard of care cell therapy treatment (Table 1). In all clinical studies, there were an expected dose-dependent prolongation of activated partial thromboplastin time (APTT), up to about 1100 seconds after 24 mg/kg i.v. Increased numbers of lymphocytes, white blood cells and especially a dose-dependent increase of HGF were recorded in the studies.

Table 1 Overview of clinical studies with ILB

| **Subjects (n)** | **Substance** | **Dose**  **(mg/kg)** | **Administration** | **Adverse Events** | **Study phase,**  **Name,**  **Eudract no.** |
| --- | --- | --- | --- | --- | --- |
| Healthy subjects (34) | ILB  Heparin as control | 4.5-15.7 | *i.v.* bolus (1.5 mg/kg) +  20 min (3 mg/kg) infusion + 5 h (~9 mg/kg) infusion | Well-tolerated. Two subjects reported  hypersensitivity  reaction. | Phase I,  LMW-DS-101, 2006-005193-42 |
| Diabetes Type 1 patients (10) | ILB  Heparin as control | Up to 18.3 | *i.v.* Bolus (1.5 mg/kg) + 20 min (3 mg/kg) infusion + 5 h (max 13.8 mg/kg) infusion | No SAEs related to ILB. ILB is as safe and effective as heparin standard therapy. | Phase II study,  CIT-01^1^, 2008-001210-25 |
| Healthy subjects (24) | ILB | 3-24 | 10 min *i.v.* infusion | All doses including 24 mg/kg are evaluated as safe and well tolerated. | Phase I/II,  LMW-DS-102, 2011-004111-23 |
| Healthy subjects (3) | ILB    G-CSF (filgrastim) | 18  0.01 | 10 min *i.v*. infusion  *s.c.* injection, once daily for 5 days | ILB 18 mg/kg in combination with filgrastim treatment is evaluated as safe and well tolerated. | Phase I/II,  LMW-DS-103, 2014-000659-10 |
| Healthy subjects (12) | LMW-DS,  ILB  (5 kDa) | 6 | Single *s.c.* injection +  Single *i.v.* injection | s.c. administration of ILB 100 mg/ml is considered safe, and with approx. 88 % bioavailability. | Phase I,  TM-104  2016-004468-20 |

^1^ TikoMed AB was IMP supplier. The study was sponsored by the National Institute of Health (NIH, USA).

Specific risks related to the treatment with ILB in this study are local injection-site reactions and hypersensitivity reactions:

In a clinical trial, two healthy volunteers reported mild and transient hypersensitivity reactions, which was judged to have a causal relationship with ILB administration. No actions were taken to treat the events, since the reactions stopped spontaneously. Forty-two healthy subjects have been dosed with approximately 6-16 mg/kg ILB without concomitant treatment with antihistamines, out of which two showed hypersensitivity reactions. As the hypersensitivity reaction was mild and transient, and occurred in only two subjects, treatment with antihistamines will not be included in this study.

The local tolerance of s.c. administration was evaluated in a phase I study in 12 healthy volunteers receiving 2-3 s.c. injections (each approx. 2 ml) of 100 mg/ml ILB in the abdomen (6 mg/kg). The local tolerability showed mild effects after 10 minutes in terms of pain, pruritus, erythema and oedema. The effects were transient and had normalised at 30 minutes or 4 hours after the injection.

In toxicology studies in rats, it has been shown that LMW-DS compounds – including ILB – had the potential to induce lung toxicity and respiratory dysfunction. To address this issue, a number of complementary toxicological studies have been performed in rats, mice and monkeys, and lung function has been studied carefully in the clinical studies with ILB. The conclusion is that the effects observed on the lungs in rat seem to be species related, as it is not seen in the nonclinical studies in mice or monkeys, and neither in previous clinical studies. However, due to the lung findings in the rat, the lung function will be monitored in the planned clinical study with intermittent forced vital capacity (FVC) respiratory tests.

Toxicology studies have been performed in both male and female rats and monkeys but as there are no data available at this stage on reproductive toxicology, all included study subjects – and their partner – of childbearing potential must use adequate double contraceptive protection during the study (Visit 2 to Visit 9). A woman is considered of childbearing potential (WOCBP) i.e. fertile, following menarche and until becoming post-menopausal – as defined as no menses for at least 12 months without alternative medical cause – or permanently sterile through hysterectomy, bilateral salpingectomy and bilateral oophorectomy. A man is considered fertile after puberty unless permanently sterile by bilateral orchidectomy.

ILB prolongs APTT in a dose-dependent manner, and after prolonged treatment in humans with a similar compound, but with higher molecular weight, thrombocytopenia has been observed. Both these effects might lead to bleeding complications. Despite this, provoked (IVY method) or spontaneous bleedings have not been observed in any of the hitherto performed clinical studies with ILB and are not expected to occur in this study, except possibly at the injection site.

ALS is a terminal disease where most patients die of respiratory muscle weakness less than 3-5 years from symptom onset. As there is yet no cure for ALS, and only one drug on the market that slightly prolongs the survival, there is for ALS patients a potential major benefit for developing a drug that may slow or reverse the disease progression.

Taken together, the data from nonclinical toxicity studies performed with ILB in mice, rats and monkey, data from studies in healthy subjects and diabetes patients, and additional information obtained from the literature with similar substances, indicate that the proposed dose and administration route in the protocol can be used in the present investigation without safety concerns.

For more detailed information about the toxicological and clinical data, refer to the Investigator’s Brochure (IB).

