# INVESTIGATIONAL PLAN

## Study design

This is a single-centre, open single-arm study where the safety, tolerability and efficacy of subcutaneously (s.c.) administered ILB will be evaluated in patients with Amyotrophic Lateral Sclerosis (ALS). There will be 10 visits to the clinic: 1 2-part screening visit (Visit 1a and Visit 1b), 5 IMP administration visits (Visit 2 to Visit 6) and 3 follow-up visits (Visit 7 to Visit 9). Each individual patient’s study participation will be approximately 4 months, including the screening and follow-up visits.

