## Overall study procedures

Subjects will be screened for eligibility according to pre-defined criteria (see section 9.3 and 9.4) within 30 days prior to first administration of IMP (Visit 1a; day -30 to -7). If eligibility is confirmed at Visit 1a, the patients will return at Visit 1b (day -23 to -1) for collection of CSF and blood for analysis of NFL and other biomarkers of neurological disorders (see 11.4.2), and – if consented by patient – exploratory purposes (see 11.5). If it is found to be appropriate by patient or Investigator, the screening tests can be performed over several visits to avoid too strenuous strain on patient and next of kin.

Each subject will receive oral and written information about the study and the planned investigations and will have to give his or her signed and dated informed consent before any study-related procedures are initiated. On recruitment to the study, the patients will be evaluated for inclusion and exclusion criteria, and undergo a baseline assessment to include demographics, medical history, concomitant medication, vital signs, physical examination (including weight and height), ECG, haematology, and clinical chemistry. Patients will also complete a baseline assessment on the ALS Functional Rating Scale (ALSFRS-R), Norris rating scale and a quality of life assessment (Appendix 2-5). The patients will during 5 visits be administered ILB 1 mg/kg per week (Visit 2 to Visit 6), followed by 3 follow up visits (Visit 7 to Visit 9) over 10 weeks after the last dose. During the clinical trial, the patients will undergo regular assessments for safety and efficacy parameters.

The overall schedule of events for the study is presented in Table 2. For the visits with critical time points for study assessments, detailed schedule of events are presented in Table 3 (Visit 2 and Visit 6) and Table 4 (Visit 4). The procedures for all study assessments are described in detail in section 11.

Table 2 Schedule of events

| **Visit** | **1a** | **1b** | **2** | **3** | **4** | **5** | **6** | **7** | **8** | **9** |
| --- | --- | --- | --- | --- | --- | --- | --- | --- | --- | --- |
|  | Screening | Screening | Dosing^7^ | Dosing^7^ | Dosing^7^ | Dosing^7^ | Dosing^7^ | Follow-up | Follow-up | End of study  follow-up |
| **Day** | -30 to -7 | -23 to -1 | 1 | 8 | 15 | 22 | 29 | 36 | 50 | 99 |
| **Time window (days)** |  |  |  | ± 3 | ± 3 | ± 3 | ± 3 | ± 3 | ± 7 | ± 7 |
| Informed consent | X |  |  |  |  |  |  |  |  |  |

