# STUDY POPULATION

## Screening log

Potential study subjects will be assessed for inclusion into the study at an initial screening visit. A screening number will be allocated to each patient. Investigators must keep a record of all screened subjects even if they were not subsequently included in the study. This information is necessary to verify that subjects were selected without bias. The reason for screen failure should be stated for all subjects screened but not included. The reason for withdrawal should be stated for all subjects included but not completed.

A patient may be rescreened. If a subject cannot receive the planned dose of IMP within 30 days after screening (*i.e.*, the time interval between signing informed consent until dose administration) the subject should be rescreened before proceeding in the trial. A result from CSF sampling at Visit 1b will be valid for 6 months.

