## Exclusion criteria

Subjects must not enter the study if any of the following exclusion criteria are fulfilled:

1. Unable to understand information about the study or are expected not to collaborate with the study team.
2. Concurrent serious disease, other than ALS, at the discretion of the Investigator.
3. Pregnancy.
4. Patients of childbearing potential not willing to use adequate double contraception^[[1]](#footnote-2)^ with < 1% failure rate after the screening visit until the last visit.
5. Addiction to drugs or alcohol.
6. Confirmed HIV, hepatitis B or hepatitis C.
7. Known bleeding disorders or abnormal bleeding events.
8. Treatment with anticoagulant drugs warfarin and novel oral anticoagulants (NOAC) within the last 14 days prior to screening.
9. Treatment with Riluzole or Lamotrigine within the last 28 days prior to study drug administration.
10. Hypersensitivity to dextran sulfate.
11. Poor venous access.
12. Patients with clinically significant abnormal PK-INR, fibrinogen, von Willebrand factor and activated partial thromboplastin time (APTT) at screening.

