### Criteria for permanent withdrawal

A subject will be permanently withdrawn from the study for the following reasons:

- Withdrawal of informed consent
- in case of pregnancy, planned pregnancy or non-compliance with set requirements for contraception
- if treatment with anticoagulants warfarin/NOAC is necessary
- concomitant treatment with Riluzole or Lamotrigine

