## Demographics and other baseline characteristics

### Informed consent

Information about the aims and procedure for the planned investigation, including information on contraception and medication, will be presented to the patient. Signed informed consent must be obtained before any screening procedures are initiated at Visit 1a.

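### Section 6.4 mandates double contraception only from the day of first dose, while exclusion criterion 4 starts it after screening, 7 to 30 days earlier if counted from Visit 1a (minor)

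*Protocol*

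**What the plan says.** Section 6.4 (Risk and benefit assessment) notes that there are no reproductive toxicology data. It therefore requires that subjects of childbearing potential, with their partners, "must use adequate double contraceptive protection during the study (Visit 2 to Visit 9"). This is the only sentence in the protocol that imposes actual use.

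Exclusion criterion 4, worded alike in the synopsis and section 9.4, shuts out patients of childbearing potential who are unwilling to use such contraception "after the screening visit until the last visit". It tests willingness at entry.

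Section 9.6.3 lists among the reasons for permanent withdrawal "in case of pregnancy, planned pregnancy or non-compliance with set requirements for contraception". It gives no window and no cross-reference.

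The screening visit is not a single date. Section 8.1 describes "1 2-part screening visit (Visit 1a and Visit 1b"). Section 8.3 places the first part "within 30 days prior to first administration of IMP (Visit 1a; day -30 to -7") and then says "the patients will return at Visit 1b (day -23 to -1"). Section 9.1 explains its 30-day limit after screening as "the time interval between signing informed consent until dose administration", and section 11.2.1 states: "Signed informed consent must be obtained before any screening procedures are initiated at Visit 1a".

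The Visit 2 window is not an isolated slip in section 6.4. The discontinuation procedures in section 9.6 use the same Visit 2 to Visit 9 period for following up pregnancies in patients or partners.

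**The concern.** One rule has two start points, and nothing in the protocol says which governs. The looser start sits in the only sentence that makes use compulsory, and it coincides with the first injection.

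Taken literally, a woman of childbearing potential need not use contraception in the days before Visit 2. A conception in that interval could be too recent to show in the urine test taken that day, and she would then be dosed. The compound has no reproductive toxicology data, which is the reason section 6.4 gives for having the rule.

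The gap matters mainly for female patients. No drug is given before Visit 2, so a conception fathered by a male patient before that visit precedes any exposure.

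**Working it through.** **Inputs.** Visit 1a is day -30 to -7, Visit 1b is day -23 to -1 and Visit 2 is day 1 (section 8.3 and Table 2). Visit 3 is day 8 ± 3, with at least 4 days between administrations (Table 2). Planned enrolment is 15 patients (section 9.2). The protocol states no figure for the gap, so there is none to reproduce.

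**Difference in start.** Section 8.3 equates 30 days before first dose with day -30, so I assume no day 0. The interval from day -d to day 1 is then d days.

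| Start read into exclusion 4 | Days before Visit 2, no day 0 | If a day 0 is counted (add 1) |
| --- | --- | --- |
| Visit 1a (day -30 to -7) | 7 to 30 | 8 to 31 |
| Visit 1b (day -23 to -1) | 1 to 23 | 2 to 24 |

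The Visit 1b range is nominal. Section 9.1 allows rescreening and keeps a Visit 1b CSF result valid for 6 months, so an earlier Visit 1b can lie well outside 23 days. The Visit 1a range is bounded by the 30-day limit in section 9.1, provided that limit is counted from the latest screening.

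**What the pregnancy tests cover.** Women of childbearing potential have a urine test at Visit 1a and at every visit from 2 to 9 (Table 2; section 11.2, Pregnancy). At Visit 2 it is a pre-dose assessment (Table 3). Section 10.1 places dosing after the other assessments of the visit, so the test should precede the injection at every dosing visit.

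**What can slip through.** Let L be the number of days after conception during which the urine test stays negative. The documents give no value for L. Under the section 6.4 window, conceptions that are both unguarded and undetected at Visit 2 fall in an interval of min(L, gap) days. That is 0 if L is 0, and at most the whole gap, up to 30 days counted from Visit 1a. The next test is at Visit 3, between day 8 - 3 = 5 and day 8 + 3 = 11, which is 4 to 10 days after the first dose. A conception missed at Visit 2 therefore means at least one exposed dose, and more only if the Visit 3 test also misses it.

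**After harmonising.** With the same start in both texts the difference is 0 days.

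**The case against.** The strongest reply is that the two texts do different jobs and are compatible. Exclusion 4 screens for willingness and section 6.4 governs use, and a patient who does what exclusion 4 describes automatically meets section 6.4. Both cover every day from first dose to Visit 9. Contraception information is given at Visit 1a, and the patient information may name a start date. Pregnancy is itself an exclusion, is tested at each visit listed above, and stops treatment. A lenient reader could also take the exclusion 4 wording to mean from the next visit onward, which is Visit 2 if screening ends with Visit 1b.

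Most of this stands and sets the grade. It does not remove the point. Willingness at entry does not oblige use, and the sentence that does oblige it begins on the day of first dose. The lenient reading is not the literal one. Repeat testing limits exposure but cannot undo the first dose.

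A reader might also infer that a woman willing at screening, who used no contraception before Visit 2, could be dosed under section 6.4 and then permanently withdrawn under exclusion 4. The documents do not support that. A willingness criterion met at screening is not breached by later non-use. Since section 6.4 is the only use requirement, it is the natural meaning of the set requirements in section 9.6.3.

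**Conclusion.** The inconsistency is real and minor. The compulsory window opens 7 to 30 days later than the eligibility window if screening means Visit 1a, or nominally 1 to 23 days later if it means Visit 1b. The consequence is a small safety gap: a very early conception in a female patient could pass the Visit 2 test and be exposed to at least one dose.

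This rests on three assumptions: no day 0, a literal reading of both texts, and a urine test that does not detect the most recent conceptions. The number of women of childbearing potential among the 15 planned patients is not stated. If the site works to exclusion 4 in practice, the gap is zero. No endpoint, estimate or analysis set is touched.

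**What to change.** - **Section 6.4:** replace the bracketed Visit 2 to Visit 9 period with *from Visit 1a until the last visit (Visit 9)*, at least for female patients.
- **Exclusion criterion 4 (synopsis and section 9.4):** use the same visit label in place of the general reference to the screening visit.
- **Section 9.6.3:** refer to that window as the set requirement.

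Visit 1a is the better anchor. Consent, contraception information and the first pregnancy test all fall there, section 9.1 already counts from consent, and the date is not loosened by a carried-over Visit 1b sample.

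The cost is wording in these places, with no added visit or test. The change reduces the chance of dosing in a very early undetected pregnancy but does not eliminate it, since a conception shortly before Visit 1a or a contraceptive failure remains possible.
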